### 2.7 Intelligent system development

Considering both the model performance and the model interpretability, the intelligent exercise prescription recommendation system will be developed based on some machine learning models with both good interpretability and high performance. Figure 2 depicts an example of this intelligent system. It is noteworthy that our designed intelligent system will explain why it recommends specific exercise prescriptions.

**FIGURE 2 F2:**
[figure not shown]
A demonstration of the intelligent system of exercise prescription.

## 3 Discussion

All cancer patients need to consider a multidisciplinary approach during treatment, which includes physical training, psychological support, and lifestyle advice (26). The concept of cardio-oncology rehabilitation has been introduced by both the American Heart Association and the American Cancer Society (64). Cardio-oncology rehabilitation is to identify PLWC who are at high risk for cardiac dysfunction as well. Physical activity intervention, that is exercise prescription, is an important component of cardio-oncology rehabilitation and can prevent or moderate cardiovascular events in cancer patients or survivors. It has been demonstrated that heterogeneous responses to the same physical training can enhance cardio-respiratory fitness in cancer therapy (65). There is some theoretical and experimental evidence as to why physical exercise can help reduce cardiovascular events in cancer patients or survivors. For example, the so-called “cancer-induced cardiac cachexia,” which refers to a multi-organ/tissue syndrome affecting the brain, liver, and heart, can exist in cancer patients because of the tumor environment (66). Previous studies have revealed that physical exercise can restore muscle strength and improve endurance, thus counteracting cardiac cachexia (67). Exercise prescription can act as an aid and therapy for cardio-oncology preventive care. Therefore, our study on interpretable machine learning of exercise prescription for cardio-oncology prevention is of significance.

Some limitations of our study need to be mentioned. First, only PLWC in cancer Stage I or cancer survivors from cancer Stage I are taken into account. Although considering more participants (e.g., expansion to Stage II or Stage III) may improve our approach’s coverage, we decide to focus on participants with milder intensities of cancer. Second, there is always a trade-off between model interpretability and model performance. Black-box deep learning models may outperform explainable machine learning models in evaluation metrics such as accuracy and area under curve (AUC). Therefore, we plan to adopt both in this study and select a balanced one for intelligent system development. Third, we will only employ internal cross-validation methods in training and testing as an initial validation choice. To fill in this gap, after the interpretable machine learning-based intelligent system of exercise prescription has been developed and used in real case for a period, we will then conduct a quasi-experimental trial for external validation in another study, just like other machine learning-based medical studies did for external validation (68–70). Furthermore, with external validation and more dataset in the future, we can continuously update the intelligent system of exercise prescription through dynamic optimization of parameters of the interpretable machine learning model.

In conclusion, physical exercise is a promising interventional strategy for cancer patients or survivors during and after medical treatment and may also be effective in counteracting some adverse effects of the tumor environment or drugs on their cardiovascular system. When prescribing exercise, we need to take the cancer patients’ or survivors’ individual characteristics, cancer drugs/medications, personal lifestyle history, and health-related physical fitness into consideration. Such a tailored exercise prescription process can be learned by interpretable models using machine learning approaches and can generate an intelligent recommendation system of exercise prescription for cardio-oncology preventive care in the future.

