### 2.6 Data analysis and interpretable learning

Effective exercise prescriptions will be selected based on pre- and post-intervention data analysis of CVD-related items. For example, if the blood pressure variability decreases or at least does not increase, the exercise prescription can be considered effective. We will employ interpretable machine learning models to the learnings on exercise prescription recommendations for all effective prescriptions.

Demographics, cancer-related information, exercise habits and lifestyle, health-related physical fitness will be input variables, while frequency, duration, and intensity of exercise prescription will be output variables. We formulate the prescription learning process as a machine learning classification task. Explainable machine learning models such as logistics regression, support vector machine, decision tree, random forest, k-nearest neighbor, and naive Bayes classifiers will be utilized. Specifically, in the logistics regression machine learning model, the estimated values of coefficients and their standard deviations, *P*-values, and 95% confidence intervals, will provide us with the interpretability. The process of feature selection and kernels when using support vector machine may reveal the model interpretability (55). Figure presentation of trees and importance ranking of features for decision tree and random forest can lead to good explanations (56). In k-nearest neighbor algorithm, showing the k-nearest neighbors might also be explainable (57). As for Naive Bayes, it can be interpreted on the modular level and the conditional probability, then thus it will be very clear for us to understand how much each feature contributes toward a certain class prediction (58). Generally, these machine learning models may all have good potential for interpretability.

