Some deep learning models will also be employed to evaluate the classification performance (accuracy, precision, recall, F-1 score, area under curve) in fivefold cross-validations, comparing them with the above-mentioned explainable machine learning models. Explanations of deep neural networks can be challenging (59), and hence to ensure that our deep learning models (convolutional neural networks, eXtreme gradient boosting, multilayer perceptron, deep residual network, DeepGBM) are more interpretable, an explainability tool named SHapley Additive exPlanations (SHAP), (60) will also be included. Recent advances in interpretability study for deep learning models have demonstrated the explainable potential for such models utilizing SHAP. For example, Zhao et al. proposed a novel SHAP scores computing algorithm for convolutional neural networks in classification (61). Meng et al. developed an integrated framework with better interpretability based on SHAP and eXtreme gradient boosting (62).

Since the intervention duration will be 2 years, there might be a great chance of loss-to-follow-up. Therefore, we set our sample size as 600 instead of 580, to cope with a higher loss rate or lower effectiveness rate than our initial estimations. If the final sample size for machine learning modeling still fails to reach the minimum bound (18), we will employ some few-shot learning algorithms (63) in such small size machine learning task to deal with this potential problem.

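### The model for the system is chosen partly on fivefold cross-validated performance, and no separate estimate is named for the chosen model, so its reported performance will tend to be optimistic

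*Protocol article*

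**What the plan says.** **Candidates.** Section 2.6 of the Protocol article lists six interpretable classifiers: "Explainable machine learning models such as logistics regression, support vector machine, decision tree, random forest, k-nearest neighbor, and naive Bayes classifiers will be utilized". The list is given as examples, so six is a minimum. The same section adds five models under deep learning: "convolutional neural networks, eXtreme gradient boosting, multilayer perceptron, deep residual network, DeepGBM". That makes 11 named models.

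**Comparison.** Section 2.6 evaluates "classification performance (accuracy, precision, recall, F-1 score, area under curve) in fivefold cross-validations" and compares the two families there. No other resampling scheme is named.

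**Choice.** Section 2.7 bases the system on models that combine interpretability with high performance. The limitations in section 3 say of the two families: "we plan to adopt both in this study and select a balanced one for intelligent system development". No weighting of the two criteria is given.

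**Validation.** Section 3 states: "we will only employ internal cross-validation methods in training and testing as an initial validation choice". External validation is left to another study, after the system has been "developed and used in real case for a period, we will then conduct a quasi-experimental trial for external validation".

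**Sample size.** Section 2.3 aims for at least 200 records for modelling, from 600 recruits, assuming 53% retention and 65% of prescriptions judged effective.

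**The concern.** A cross-validated score is a fair, if noisy, estimate for a model fixed beforehand. Once several models are compared on such scores and a high one is favoured, the favoured score is high partly by chance. Reporting it as the performance of the chosen model carries that chance forward. Any tuning or feature selection done outside the folds would add to it.

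Two things are at stake. The first is the performance figure itself, which is a main product of the study. The second is the choice between an interpretable and a black-box model, which section 3 presents as a trade-off. At this sample size a gap of a few points between two models can be noise plus selection, and acting on it could give up the interpretability that the study sets out to deliver.

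The limitations paragraph acknowledges that external validation is lacking. It does not mention optimism from model selection, which can be dealt with inside this study.

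**Working it through.** **Step 1. Records available (section 2.3).**
- The plan's own figure: 200 / 0.65 / 0.53 = 580.55, which reproduces.
- Expected from 600 recruits: 600 × 0.53 × 0.65 = 206.7, about 207 records, or about 41 per fold (206.7 / 5).

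**Step 2. Number of candidates (section 2.6).** 6 + 5 = 11.

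**Step 3. Noise in one accuracy.** The documents give no expected accuracy. Assuming 60% and n = 200, SE = √(0.60 × 0.40 / 200) = 0.0346, about 3.5 points.

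**Step 4. Optimism if the top scorer of 11 is taken.** I simulated 200 records classified by 11 models. Each model's correct or incorrect result comes from a latent normal variable, and the correlation of that variable between models is assumed to lie between 0.3 and 0.9. Optimism is the mean of (observed accuracy of the top scorer − true accuracy of that same model). True accuracies are either all 60%, or vary around 60% with the SD shown.

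| SD of true accuracies | corr. 0.3 | 0.5 | 0.7 | 0.9 |
|---|---|---|---|---|
| 0 (all equal) | 4.9 | 4.5 | 3.9 | 2.9 |
| 3 points | 3.5 | 3.1 | 2.5 | 1.6 |
| 5 points | 2.5 | 2.1 | 1.7 | 1.0 |
| 10 points | 1.2 | 1.1 | 0.8 | 0.5 |

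Entries are percentage points. Equally good models give about 3 to 5 points. Models that truly differ give about 0.5 to 3.5, because a real front-runner is then more often picked on merit.

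**Step 5. Sensitivity to the assumed accuracy.** A normal approximation with equally good models, n = 200 and the correlation placed on the accuracies themselves (0 to 0.9) gives 1.7 to 5.5 points at 60%, 1.6 to 5.1 at 70% and 1.4 to 4.5 at 80%. The assumed accuracy matters less than the correlation and the spread. The two correlation scales differ: a latent correlation of 0.9 corresponds to about 0.71 between accuracies, where this approximation gives about 3.0 points at 60%, in line with the 2.9 in the table.

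**Step 6. What the stated rule does to these figures.** Step 4 takes the top scorer outright. The article weighs interpretability as well, so step 4 is an upper case for each scenario. If interpretability alone decided, the chosen model's score would not have been selected for being high, and this part of the bias would be about zero.

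**The case against.** **Shared selection and reporting is inferred.** The article does not say that a single non-nested loop does both. It speaks of cross-validation in the plural, nested cross-validation is itself an internal method, and an article may leave such detail to a fuller document. This stands as a limit on certainty: a reader might infer that the plan declares a shared loop, and it does not. It does not remove the point. The article itself fixes the scheme, the metrics, the use of performance in the choice and the restriction to internal cross-validation, and followed as written these give no separate estimate for the chosen model.

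**The top scorer need not win.** Section 3 seeks a balanced model, and section 2.7 speaks of models in the plural. This stands. A reader might take 3 to 5 points as the expected bias, but that needs 11 equally accurate models and a choice on score alone. Equal accuracy is unlikely for methods as different as naive Bayes, a single tree and a convolutional network.

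**The optimism is modest.** In most scenarios where the models truly differ it is below the 3.5-point SE of one accuracy. That is right, but the SE is two-sided noise whereas selection pushes one way.

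**External validation is disclosed and planned.** This also stands; the lack of it is an acknowledged limitation. A reader might go further and infer that patients will be managed on the strength of an inflated figure. The documents do not support that: the conditions of real use are not described, no performance threshold for release is given, and no performance has yet been reported. Only the order, use first and external validation later, is explicit.

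**Conclusion.** The point holds in a measured form. On the natural reading, the cross-validation that helps choose among at least 11 models also supplies the performance reported for the chosen one, and that figure will be too high to the extent that performance drives the choice.

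The size is roughly 0.5 to 5 percentage points of accuracy where the top scorer is taken, falling towards zero as interpretability takes over the decision. This rests on assumptions that the documents do not supply: accuracy near 60%, the correlation between models, and the spread of their true accuracies. The article gives the direction but cannot fix the size. Tuning and feature selection are not included in these figures.

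The order of real use and external validation is a secondary matter. It is explicit, but it concerns later work. Section 3 presents external validation as filling the gap left by internal validation, yet puts it after use has begun.

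**What to change.** 1. In section 2.6, specify repeated nested cross-validation. Feature selection, tuning and the choice among models take place in the inner folds. The outer folds serve only to report the performance of the whole selection procedure. The selection part of the bias is then about zero.
2. Fix in advance how performance and interpretability are traded off, including which of the five metrics decides. One reasonable convention among several is the simplest interpretable model within one SE of the best.
3. In section 3, reconsider placing real use before external validation, or state that until then the system's performance is only internally validated.

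Cost: items 1 and 2 need computing time and some wording, and no further participants. The reported performance will probably be slightly lower. If the order in item 3 is changed, real use starts later.

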## Ethics statement

The protocol has received approval from the Ethics Inspection of the Ethical Review Board of Guangzhou Sport University (Ethics Approval ID: 20232022-41). The patients/participants provided their written informed consent to participate in this study.
